**III. Summary**

In malaria endemic areas in sub-Saharan Africa, pregnant women, especially primi - and secundigravidae, are more likely to have placental and peripheral parasitemia with *Plasmodium falciparum* than non-pregnant women. Adverse consequences of malaria in pregnancy include maternal anemia, and low birth weight of the new born. Low birth weight is known to be the most important risk factor for infant mortality.

Due to widespread and high-grade chloroquine resistance, sulfadoxine-pyrimethamine (SP) is rapidly replacing chloroquine in East Africa as first line drug for treatment of malaria. Recent studies have shown that intermittent preventive treatment (IPT) with SP during pregnancy can mitigate the adverse effects of malaria in pregnancy. In 1998 The Kenya National Malaria Control Program adopted the strategy of IPT with SP to be delivered as one treatment dose of SP at the first antenatal clinic visit occurring after the first trimester, and a second treatment dose of SP at the beginning of the third trimester (between 28 and 34 weeks).

The action of SP is based on inhibition of parasite enzymes in the metabolism of folic acid. However, in vitro studies indicate that folic acid can antagonize the antimalarial parasite activity of SP. Furthermore, in one recent West African study, supplementary folic acid compromised the antimalarial efficacy of SP in children with acute malaria aged 6 months to 12 years.

Folic acid requirements are increased during pregnancy, and supplementation with folic acid in pregnancy is recommended. Although in most countries a daily supplementation of 400 to 600 micrograms is considered sufficient, for logistical reasons the daily recommended dose in Kenya is 5 mg of folic acid during pregnancy. It is unknown whether folic acid supplementation might compromise the efficacy of IPT with SP in pregnant women living in malaria endemic areas.

We propose a placebo-controlled study to address this question. Parasitemic pregnant women visiting the ANC of Nyanza Provincial General Hospital, Bondo District Hospital, or Siaya District Hospital will be randomized to receive either SP with folic acid 5 mg, or SP with folic acid 400 g, or SP and placebo. The placebo and the folic acid 400 g will be given for two weeks, and then be replaced by folic acid 5 mg. Data from this study will be useful to evaluate the need for a modified regimen of folic acid supplementation recommendation in areas where IPT with SP is used.

**IV. Introduction and background**

**Introduction**

Malaria in pregnancy is a problem involving more than 20 million women of childbearing age per year in sub-Saharan Africa (United Nations Children’s Fund, 1998). Compared to non-pregnant women, pregnant women more frequently harbor *Plasmodium falciparum* in the peripheral and placental vascular space, and experience higher density infections. Although in malaria endemic areas severe clinical malaria in pregnancy is not common, this increased frequency and density of *P. falciparum* infection is associated with lower maternal hemoglobin, fetal growth retardation and prematurity, particularly in primigravidae (Brabin 1983, Menendez 1995, Steketee et al, 1996a). Low birth weight is known to be the most important risk factor for infant mortality (McCormick, 1985). Recent estimates suggest that among pregnant women in malaria endemic areas, 3-15% of anemia, 8-14% of low birth weight and 3-8% of infant mortality could be attributed to malaria (Steketee et al, 2001).

Approaches to reduce the impact of malaria in pregnancy have included weekly chemoprophylaxis with chloroquine; however, the feasibility of such a program was compromised by logistical constraints and the bitter taste of the drug (Kaseje et al, 1987). With increasing resistance of *P*. *falciparum* to chloroquine, new approaches were evaluated.

In studies in sub-Saharan Africa, intermittent preventive treatment (IPT) with sulfadoxine-pyrimethamine (SP), one dose in the second trimester and one dose in the early third trimester (28-34 weeks), was found to reduce the prevalence of parasitemia (Schultz et al, 1994, Parise et al, 1998), maternal anemia (Shulman et al, 1999) and low birth weight (Parise et al, 1998, Verhoeff et al, 1998, Rogerson et al, 2000). Studies that reported information on side effects documented that IPT was well tolerated; side effects, if they occurred, were mild and no severe adverse skin reactions were seen. The use of SP was not associated with neonatal complications, like kernicterus in the newborn, or congenital abnormalities (Verhoeff et al, 1998, Parise et al, 1998).

Currently, the World Health Organization recommends that pregnant women in malaria endemic areas receive IPT: the administration of full, curative-treatment doses of an effective antimalarial drug at predefined intervals during pregnancy (WHO 2000). In areas such as sub-Saharan Africa with substantial chloroquine resistance, interest has focused on the delivery of SP as IPT. Besides the relatively low costs of a treatment dose in comparison with other antimalarials, SP has the advantage of being a single dose drug; the three tablets (adult dose) can be given under supervision in the antenatal clinic (ANC), leading to improved adherence over regimens requiring dosing over multiple days.

In 1993, Malawi was the first country to introduce IPT with SP for the control of malaria in pregnancy as a national policy. In 1998, Kenya adopted this policy, and more African countries are adopting or considering this approach.

**Folic acid and pregnancy**

Human beings are fully dependent on dietary sources or dietary supplements for their folate supply. Folate is an essential nutrient for cell metabolism and for the synthesis of purines and pyrimidines, components of DNA and RNA. During pregnancy, folate is necessary for normal embryonic development and growth. Recent research has demonstrated a significant increase in folate catabolism during pregnancy, with a peak in the third trimester and a sharp fall after delivery, corresponding with the period of maximal increase in fetal mass (Higgins et al, 2000). Folic acid deficiency in pregnancy has been associated with the development of fetal neural tube defects, maternal megaloblastic anemia, and low birth weight (Lumley et al, 2001, Smits & Essed 2001, Mahomed 2000). Recommendations for doses of folic acid to be taken during pregnancy differ per country and purpose.

Supplementation with folic acid around the time of conception significantly reduced the incidence of neural tube defects but folate supplementation begun after the first trimester of pregnancy is too late to prevent birth defects (Lumley et al, 2001). In the USA, the recommended dose of folic acid to prevent neural tube defects is 400 microgram per day, starting preferably one month before conception and continuing throughout the first three months of pregnancy (CDC 1992). However, a recent review recommends even 5 mg folic acid tablets daily to reduce the risk of neural tube defects (Wald et al, 2001).

A Cochrane review specifically addressing the effect of folate supplementation in pregnancy on haematological and biochemical parameters and measures of pregnancy outcome (Mohamed, 2000) reports that compared to placebo or no supplementation, folate supplementation was associated with a significant reduction in the proportion of women with low haemoglobin level in late pregnancy and megaloblastic erythropoiesis. Apart from a possible reduction in the incidence of low birthweight, folate supplementation appeared to have no measurable effect on any other substantive measures of pregnancy outcome (Mohamed, 2000).

For the prevention of folate deficiency and megaloblastic anemia in pregnancy, the recommended dietary allowance is 600 microgram per day (Food and Nutrition Board of the Institute of Medicine, USA, German Nutrition Society). International anemia treatment guidelines recommend in areas with a prevalence of anemia in pregnancy of 40%, 400 microgram folic acid in combination with 60 mg iron daily for 6 months in pregnancy, and continuing 3 months postpartum (Stoltzfus & Dreyfuss, 1997). In Kenya 5 mg of folic acid per day is recommended for prevention of anemia, to start at the first ANC and to continue until labor; 5 mg of folate was chosen because it was the lowest dose in a tablet that was available in the country (Ministry of Health, 1994). In the Kenya MOH simplified national guideline on malaria control for community resource persons, treatment of anemia in pregnant women is recommended to be three months of folic acid 5 mg/day, starting two days after any SP (Ministry of Health, 2000). The WHO recommends a delay folic acid supplementation for one week after SP to avoid an inhibitory effect on antimalarial efficacy (WHO expert committee on malaria, 2000).

The evidence available on the role of folate in reducing the risk of vascular disease, cancer and psychiatric and mental disorders is not sufficiently conclusive to be able to come up with recommendations for supplementation (The National Academy of Sciences, 2000).

**Malaria and folic acid**

There is evidence from several studies that red blood cell folate concentrations may be raised in the presence of malaria. First reported in experimental animal systems (Trager, 1959), studies on red blood cell folate concentrations in Nigerian children (Bradley-Moore et al, 1985) and in Kenyan primigravidae (Brabin et al, 1986) confirmed this association. Brabin et al (1986) suggest several explanations. Individuals with malaria who are actively hemolyzing may have an increase in reticulocytes, cells with a much higher concentration of folic acid than mature red blood cells. Other explanations are that parasites may synthesize the folate in the red blood cells, or the host may express an altered metabolism of folic acid in the red blood cell in the presence of malaria. In one in-vitro study, it was suggested that folic acid deficient persons may have some natural resistance to malaria (Brockelman et al, 1983).

If folic acid deficiency were protective against malaria, an association might be seen between malaria parasitemia and the high serum or RBC folate levels achieved with folic acid supplementation. However, this is not supported by results from several other studies. Folate status (serum and red cell folate level) was not significantly related to the density of malaria infection in a cross-sectional study in a representative sample of a rural population in South Benin (Hercberg et al, 1986). Pregnant women in Nigeria who were supplemented with high doses of folic acid (5 injections of 15 mg folic acid each, spread over 2 weeks) did not show a higher parasite prevalence or density after 2 weeks compared to a control group (Gail & Herms 1969). There was no significant difference in parasitemia between Gambian children who received folate supplementation (5 mg/day fortnightly) or placebo (Fuller et al, 1988).

If malaria parasitemia increases red blood cell folate level, treatment of malaria should result in a decrease of the red blood cell folate level, and this was reported after treatment with chloroquine in Kenyan pregnant women (Brabin et al, 1986). However, in a placebo controlled study in Gambian children aged 3 months to 4 years, fortnightly maloprim (dapsone-pyrimethamine) as prophylaxis was associated with a non-significant increase of levels of red cell folate compared to placebo (Fuller et al, 1988). In addition, a study among primigravidae in Nigeria using weekly 5 mg folic acid or placebo showed that malaria treatment and prophylaxis given in the second trimester without folic acid supplementation stabilized folic acid levels compared to pregnant women who did not receive folic acid and antimalarial treatment / prophylaxis (Fleming et al, 1968). In this study no difference in hemoglobin level was seen between folic acid supplemented and non-supplemented pregnant women. The authors postulate that treatment of malaria in pregnancy reduces haemolysis and the requirements for folic acid (Fleming et al, 1968).

**SP and folic acid**

The components of SP, sulfadoxine and pyrimethamine, act at sequential steps of the malaria parasite folate metabolism, resulting in a synergistic inhibition of parasite growth. The action is based on reversible inhibition of enzymes in the metabolism of the malaria parasite for the use of folic acid (Annex 1): sulfadoxine inhibits the plasmodial dihydropteroate synthase (DHPS) and pyrimethamine blocks the dihydrofolate reductase (DHFR). As a result, parasite growth and multiplication in red blood cells is inhibited. Because the enzymes are located in sequence on the plasmodial folate biosynthetic pathway, the selective chemotherapeutic efficacies of the individual components are potentiated. As a consequence, the dose of both components can be reduced and accordingly the risk of side effects decreased. The development of plasmodial resistance against SP may be delayed because the different components affect different enzymes (Weidekamm 1982). An association between stage of parasite development and therapeutic response has been shown for SP, whereby parasite clearance was slower when young ring form of *P. falciparum* predominated at the time of presentation (Rieckmann et al, 1987). For SP to be most effective, the parasite needs to be intracellular, and in the phase of multiplication (schizogony), when purine precursors required for nucleic acid synthesis are formed.

Although sulfadoxine-pyrimethamine is supposed to selectively block parasite enzymes, it is possible that pyrimethamine acts on human DHFR as well, and thus has the potential to induce folic acid deficiency. Pyrimethamine in combination with dapsone has been reported to cause severe megaloblastic anemia when taken in excessive amounts (Hughes & Gatus, 1979). However, mean red cell folate levels were similar in children, aged 3 months to 5 year, who received fortnightly 12.5 mg pyrimethamine and 50 mg dapsone or placebo as prophylaxis for malaria (Fuller et al, 1988). Latent folate deficiency has been reported in expatriates who took one tablet of SP a week for prophylaxis; the authors attribute this however to an effect of sulfadoxine, because decreased mean serum folate levels were not seen in expatriates using pyrimethamine only as prophylaxis (dose of pyrimethamine not reported, Sturchler & Holzer, 1980). For patients who require large doses of pyrimethamine (e.g. for treatment of toxoplasmosis) it is common to advise folinic acid supplementation to reduce this potential effect on folate metabolism. It is not likely that the relatively small amount used for treatment of malaria can induce folic acid deficiency.

Several studies have examined the effect of folic acid on the antimalarial activity of sulfadoxine and/or pyrimethamine. A small clinical study in 9 Gambian children with malaria did not detect an effect of high doses of folic acid over a short period (10 to 30 mg per day for 3 days) on the antimalarial effect of pyrimethamine (0.25 mg/kg body weight, Hurly 1959). Seventy five US marines in Vietnam hospitalized for treatment of malaria received pryimethamine 25 mg 3 times per day for 3 days and sulfisoxazole 500 mg 4 times a day for 6 days, with either folic acid (5 mg per day), folinic acid (5 mg per day), or placebo; there was no difference in parasite clearance among treatment groups (Tong et al, 1970).

Malaria parasites may not be obligatory dependent on p-aminobenzoic acid (PABA) and may also be able to utilize exogenous folate for tetrahydrofolate formation. A study on mechanisms of drug resistance in *P. falciparum* suggested that, once the parasites become resistant to sulfadoxine, they no longer use PABA for dihydrofolate biosynthesis, but that they use folic acid instead (Tan Ariya & Brockelman, 1983, Brockelman et al, 1983). Folic acid antagonized the anti-malaria activity of sulphonamide drugs in vitro (Watkins et al, 1985, Milhous et al, 1985). In the Gambia a higher malaria treatment failure rate was noted among children treated with SP and folic acid compared with children treated with SP and iron, or SP and placebo (Boele van Hensbroek et al, 1995). In the last study, the participating children, aged between 6 months and 9 years, received either SP (1.25 mg/kg pyrimethamine and 25 mg/kg sulfadoxine) and folic acid (5 mg per day for children weighing < 15 kg, 7.5 mg/kg per day for those weighing 15-20 kg and 10 mg per day for those weighing > 20 mg/kg), SP and iron, or SP and placebo. Parasitological failure rates were 10.5% (9/86) at day 7 among children receiving SP and folic acid, and 3.1% in the other groups combined (5/160, *P* = 0.04); the cumulative failure rate at day 28 was 30.1% (22/73) among the children who received SP and folic, and 16.0% (21/131, *P* = 0.02) among the children in the other groups. The authors suggest that the treatment failures may have been due to *P. falciparum* strains with pyrimethamine resistance, whereby folic acid supplementation made it possible to bypass the sulfadoxine action (Boele van Hensbroek et al, 1995).

More recent in-vitro studies into mechanisms of drug resistance of SP suggest that the interaction may be more complicated and that the synergy between pyrimethamine and sulfadoxine may be affected by folate levels (Wang et al, 1997, 1999). It is suggested that in parasites using exogenous folate efficiently, sulfadoxine inhibition can be restored by pyrimethamine. As the mean half time of sulfadoxine is about twice that of pyrimethamine, their model predicts that, during a period of 3-13 days, when pyrimethamine exceeds a certain blood level, folate utilization will be prevented; this time period will depend upon drug elimination rates and parasite genotype. Once the pyrimethamine concentration drops below this level, any surviving parasites can resume the use of exogenous folate. The degree to which pyrimethamine can inhibit folate utilization could be expected to be dose-dependent and the research group suggest that “loading patients with very large amounts (5-10 mg) of folate daily will inevitably reduce the ability of pyrimethamine to maintain dihydropteroate synthetase as a relevant target for sulfadoxine” (Sims et al, 1999). Prediction of the fate of parasites in individual cases is complicated by host factors, such as the degree of immunity, variation in folate levels and drug metabolism, and parasite factors such as their genotypes involved in drug resistance to SP and their efficiency in using exogenous folate.

**Drug resistance genes and SP**

The development of drug resistance by *P. falciparum* has been attributed to a combination of factors: human migration, heavy malaria transmission and sustained and often haphazard use of drugs. Watkins and Mosobo postulated that selective pressure for resistance is a function of a long elimination half-life of a drug (Watkins & Mosobo 1993). Both components of SP have a long half-life (about 100 hours for pyrimethamine and 200 hours for sulfadoxine), and this may result in the selection of drug resistant mutations at non-inhibitory drug levels during the drug-elimination phase. Simple and reliable methods for drug resistance testing could be provided by molecular assays when is known which genes are involved. Several mutations in parasite DHFR and DHPS have been associated with drug resistance in in-vitro studies, e.g. mutations at codon 108 and 59 for DHFR. In a study in Malawi, infections caused by parasites with 3DHFR mutations and 2DHPS mutations (the quintuple mutant) were associated with SP treatment failure. Although the presence of a single DHFR mutation (Arg-59) with a single DHPS mutation (Glu-540) predicted the presence of the quintuple mutant, this model needs to be validated in other settings (Kublin et al, 2002), making the determination of mutations not yet available as a tool for surveillance of SP resistance (Dicourte et al, 1999).

**HIV and folic acid and SP**

It has been shown repeatedly that HIV-seropositive pregnant women have a higher risk of malaria than HIV-seronegative pregnant women (Steketee *et al*. 1996b, Verhoeff *et al*. 1999). Moreover, a recent study suggested that IPT with SP showed reduced efficacy in clearing placental parasitemia in HIV-seropositive compared to HIV-seronegative pregnant women. However, no difference was observed between the two groups in the clearance of peripheral parasitemia (Parise *et al*. 1998).

HIV-infected pregnant women are more likely to be anemic compared with HIV-uninfected women ([name] et al, 2001, Friis et al. 2001). In a recent study in pregnant women in Zimbabwe, HIV-infection was a negative predictor of serum folate, and the authors suggested this may be because of reduced intake and absorption, and increased catabolism in HIV-infected pregnant women (Friis et al, 2001).

Because HIV-seropositive women as a group may have a different folic acid status (and a potential different reaction to folic acid supplementation) than HIV-seronegative women, it will be important to assess HIV-status in study participants It will also be important to confirm that no difference exists between HIV-seropositive and HIV-seronegative women in efficacy of SP for clearance of peripheral parasitemia.

**Sickle cell disease, sickle cell trait and SP**

Sickle cell trait is common among the population in the study area, and was observed in 26% of children participating in an anemia treatment study in an adjacent rural area ([name], personal communication). Sickle cell disease was prevalent in less than 1% of the children participating in the same study. Sickle cell status of participants will be important to include in this study for two reasons:

1) A lower risk of treatment failure with SP for children with sickle cell trait has been reported, so sickle cell trait may act as a confounder in the association between SP treatment failure and folic acid ([name], personal communication).

2) Women with known sickle cell disease should receive folic acid supplementation and therefore should be excluded from this study.

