**E. Procedures**

***Recruitment***

Prior to screening, the study will be explained to all eligible pregnant women and informed consent will be obtained for both the screening procedures, which include testing for HIV, and sickle cell trait, as well as for the SP-folic acid study with three arms (see also annex 2). We will explain to the woman that a decision will be made on whether she can enter the main placebo controlled SP study with three arms after the study physician has reviewed the results of her screening.

Women will be screened at the antenatal clinic at the NPGH, BDH and SDH. A history of previous and present medication use and a medical history will be taken. Body-temperature and weight and height will be recorded. A urine sample will be examined for the presence of sulfa compounds. A blood sample will be obtained by venipuncture to measure hemoglobin, and to make a thick and thin blood smear. In addition, blood will be taken for HIV-tests, electrophoresis to assess the sickle cell status of the woman, and a serum folic acid level. The HIV-status, sickle cell status, and serum folic acid level will only be determined for women who have been enrolled. For logistical reasons it will not be possible to have the sickle cell test result the same day. It is expected that most women with sickle cell disease will not qualify for enrollment because of their medical history and hemoglobin level. Women who have been enrolled but are shown to have sickle cell disease will be informed as soon as the result is available; this will be the day after enrollment or on the first follow up appointment at day 2. They will be removed from the study and provided folic acid supplementation free of charge for one month. The blood requirements for the HIV-tests and the sickle cell test are minimal, and taking this sample when taking blood for screening will save the pregnant woman an additional venipuncture if she is enrolled.

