
***Definitions:***

Documented fever will be defined as an axillary temperature of 37.5 oC. Parasitaemia will be defined as the presence of any asexual bloodstage parasite of *Plasmodium falciparum* in a thick smear after inspection of microscopic fields until 300 leucocytes have been counted. A woman will be considered HIV-seropositive if both tests are positive and HIV-seronegative if both HIV-tests are negative. In case of an inconclusive result the rapid test Capillus HIV-1/HIV-2 (Cambridge Diagnostics, Wicklow, Ireland) will be used. Women with the hemoglobin phenotype HbAS will be defined as having sickle cell trait, and women with the hemoglobin phenotype HbSS will be defined as having sickle cell disease. Anemia will be defined as a hemoglobin < 11 g/dl, and severe anemia will be defined as a hemoglobin < 7 g/dl. For analysis a hemoglobin < 8 g/dl, moderate-to-severe anemia, will be considered because studies have indicated that a hemoglobin < 8 g/dl may be an important indicator in association with malaria (Verhoeff et al, 1998). Parasitologic failure and treatment failure will be used as previously described.

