**F. Data analysis**

Data will be entered using an optical scanner. Data cleaning will be ongoing during the course of the study. The analysis will be done using SPSS and SAS. Cumulative parasite failure will be calculated by day 3, day 7, day 14, and day 28, stratified by treatment group and compared using a chi-squared test. To assess the effect of HIV-infection, the analysis will be repeated when stratified by HIV-status. Results will be presented first to the Kenya Ministry of Health and will then be presented at national and international conferences and submitted for publication in peer-reviewed journals.

F1. Interim analysis

No definite interim analysis is planned. However, drug resistance rates to SP in Africa are increasing and could potentially reach a point during this study where one would have to consider whether it is appropriate to continue giving SP to pregnant women in a clinical trial.

If overall failure rates (clinical and parasitological) reached 50% at 14 days, we plan a blinded interim analysis by treatment group. These data would be provided to a three-member independent panel (two epidemiologists, one statistician) who would review the data and advise the study team if it appropriate to continue the study. They would take into account such factors as differential efficacy between the treatment arms, as well as power to see a difference given the projected numbers of women still to be enrolled at the time of the interim analysis.

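### Sickle cell trait is typed because it may affect SP failure, but the planned between-arm analysis never uses it; a prespecified adjusted comparison would be a small, cheap gain

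*Protocol*

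**What the plan says.** Section IV, under the heading on sickle cell disease and trait, states: "Sickle cell status of participants will be important to include in this study for two reasons". The first reason is prognostic. It starts from a finding in children: "A lower risk of treatment failure with SP for children with sickle cell trait has been reported". From that finding the protocol draws its inference for this trial: "so sickle cell trait may act as a confounder in the association between SP treatment failure and folic acid". The second reason concerns the disease and not the trait: "Women with known sickle cell disease should receive folic acid supplementation and therefore should be excluded from this study". The same section gives a local trait prevalence, which "was observed in 26% of children participating in an anemia treatment study in an adjacent rural area".

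The data are then collected. Under Recruitment: "The HIV-status, sickle cell status, and serum folic acid level will only be determined for women who have been enrolled". Under Definitions the trait has its own analysis definition: "Women with the hemoglobin phenotype HbAS will be defined as having sickle cell trait".

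Section VII.F takes cumulative parasite failure by days 3, 7, 14 and 28, "stratified by treatment group and compared using a chi-squared test", and repeats this within HIV strata. It gives no role to sickle cell trait. Day-0 parasite density appears elsewhere, as an entry criterion and within the definition of early treatment failure, but not as a covariate.

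**The concern.** The protocol names a variable that could disturb its first objective, whether folic acid affects SP efficacy. It measures that variable in everyone and then specifies a comparison that cannot take it into account. HIV status, flagged in the neighbouring background section, is carried into the analysis; trait is not.

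Two things are at stake. Randomisation balances trait only on average, so a chance imbalance passes into the crude failure difference. A comparison that ignores baseline predictors of failure also gives up some precision. There is a practical consequence as well: having raised the question itself, the protocol invites readers to ask for a trait-adjusted result, and an adjusted model chosen after unblinding would be post hoc.

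**Working it through.** **Inputs from the protocol.** 200 women per arm, 25% loss, 5% v 15% failure at day 7, 80% power and 95% confidence (Section VII.D); trait prevalence 26%, observed in children (Section IV).

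**Inputs assumed.** The protocol gives only the direction of the trait effect, so odds ratios from 0.1 to 1.0 are used. It gives no effect of HIV status or parasite density on failure; the assumed odds ratios are 1.5 to 2 for HIV and 2 to 4 per log10 of density. The test is taken as two-sided at 5%.

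**The plan's own figure.** The two-proportion formula for 5% v 15% gives 141 per arm, or 160 with continuity correction. Then 160 × 1.25 = 200, the stated number. Dividing by 0.75 instead gives 141/0.75 = 188 and 160/0.75 = 214. None of this depends on covariates. Evaluable women per arm: 200 × 0.75 = 150.

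**Chance imbalance in trait.** SD of the between-arm difference = sqrt(2 × 0.26 × 0.74/150) = 0.0506, about 5.1 points. The probability of a gap over 5 points is about 32%, and over 10 points about 5%, per pair of arms.

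**What an imbalance does to failure.** Shift = imbalance × (failure without trait − failure with trait). The stratum risks are solved so that the arm averages 5% or 15%.

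| Assumed trait OR | 5% arm: without − with trait | 15% arm: without − with trait | Shift from a 10-point imbalance, split evenly between arms |
|---|---|---|---|
| 0.5 | 5.7 − 3.0 = 2.8 points | 17.0 − 9.3 = 7.7 points | 0.10 × (2.8 + 7.7)/2 = 0.5 points |
| 0.3 | 6.1 − 1.9 = 4.2 points | 18.1 − 6.2 = 11.9 points | 0.10 × (4.2 + 11.9)/2 = 0.8 points |
| 0.2 | 6.3 − 1.3 = 5.0 points | 18.7 − 4.4 = 14.3 points | 0.10 × (5.0 + 14.3)/2 = 1.0 points |

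(Gaps are taken from unrounded risks.) If the whole imbalance fell in the 15% arm at OR 0.2, the shift would be 0.10 × 14.3 = 1.4 points. For comparison, the target difference is 10 points, with standard error sqrt(0.05 × 0.95/150 + 0.15 × 0.85/150) = 0.034, or 3.4 points. At the day-28 rates quoted in Section IV from the Gambian children's study (about 16% v 30%), the evenly split 10-point imbalance gives 1.1 to 2.1 points for ORs of 0.5 to 0.2.

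**Power from trait alone.** Simulation with 40,000 runs per scenario, 150 per arm, 5% v 15%:

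| Trait OR | Chi-squared | Mantel-Haenszel stratified by trait |
|---|---|---|
| 1.0 | 84.6% | 84.5% |
| 0.7 | 84.2% | 84.2% |
| 0.5 | 84.7% | 84.8% |
| 0.3 | 84.2% | 84.6% |
| 0.2 | 84.4% | 85.1% |
| 0.1 | 84.5% | 85.3% |

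Under no treatment effect, at 5% or 15% failure, the chi-squared test rejects in 4.8% to 5.2% of runs and the stratified test in 4.8% to 5.3%.

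**Power with more covariates.** A logistic model with trait, HIV status and log10 day-0 density, at 5% v 15% and 3,000 runs per scenario, moved power from 84.1% to 85.9%, from 83.5% to 84.6%, and from 84.6% to 87.8%. With inert covariates it was 84.3% v 84.2%. At 16% v 30% the gain reached about 5 points under the strongest assumed effects. At 5% failure the logistic likelihood-ratio test was slightly liberal, with type I error of 5.3% to 6.4%.

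**Events available.** 0.05 × 150 = 7.5 and 0.15 × 150 = 22.5, so about 30 failures in a day-7 two-arm comparison.

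**The case against.** The strongest reply is that covariate adjustment of a randomised comparison is commonly left to the SAP, which is not available here. Section VII.F is a short paragraph that names a main test and does not rule out others. That would answer a complaint about silence. It does not fully answer this one, because the protocol itself names trait as a threat to the comparison, and Section VII.F already treats the use of a baseline factor (HIV status) as protocol content.

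Several further objections stand and limit the point:

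- A reader might take the word *confounder* at face value and infer that the unadjusted test is biased. It is not. Allocation is randomised, trait is fixed before allocation, and the simulated type I error stays at about 5%.
- A reader might infer that the plan ignores every baseline predictor. It does not: HIV status is used by stratification, and day-0 density helps define early failure. Density is unused only as a covariate.
- A reader might infer that typing serves no purpose if trait goes unanalysed. Excluding sickle cell disease is a separate stated reason and would need the test anyway. That reason does not explain defining HbAS, however, since women with trait stay in the study.
- Adjustment is not entirely free. With about 30 failures at day 7, a model with many terms would be unstable. SPF-Form 1b allows indeterminate and not-done results, so a complete-case model could lose women whom the chi-squared test keeps. An adjusted odds ratio is also a different quantity from the difference in failure rates on which the sample size rests.

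**Conclusion.** The mismatch between Section IV and Section VII.F is plain in the text, and it is minor. Trait and log day-0 density are collected and never used as covariates. The cost is some precision and exposure to chance imbalance, not validity.

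The power lost is under about 1 point from trait alone and roughly 1 to 5 points once day-0 density is included. A trait imbalance that occurs about once in twenty comparisons would move the day-7 failure difference by about 1 point or less, against a target of 10. These sizes rest on assumed odds ratios, and on a 26% prevalence taken from children and not from the trial population. The documents do not support reading this as a flaw in the main test, as a reason to replace it, or as a material shortfall in the planned power.

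**What to change.** In Section VII.F, keep the chi-squared test and prespecify beside it one covariate-adjusted comparison of failure by arm. Two forms would serve:

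- a Mantel-Haenszel comparison stratified by sickle cell trait and HIV status; or
- a parsimonious logistic model with arm, trait, HIV status and log day-0 parasite density, standardised to the risk scale.

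Report an adjusted risk difference with its 95% CI, so that the result stays on the scale of the sample size calculation. Keep women with missing or indeterminate trait or HIV results through a missing category. At day 7 hold the covariates to this short list because failures are few. The stratified form is the safer choice there, given the slight liberality of the logistic likelihood-ratio test at low failure rates.

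In Section IV, replace *confounder* with *prognostic factor*.

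The cost is a few sentences and a little more analysis. No new data are needed, and the sample size does not change.
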